#### Data management and confidentiality

Questionnaires will be answered online. The screening is the only time participants enter personal contact information. In the subsequent assessments and questionnaires, participants are identified by a random computer-generated code. Other than the study coordinators, only therapists and clinical raters know the participant’s name. The anonymized data is stored in an encrypted folder on a protected research server at Goethe University Frankfurt. There is also a separate encrypted list that contains only contact information and the code so that participants can be contacted if needed. This list is deleted after the study, so that only the codes with the assigned data remain. The program R is used to analyze the data. The results of the study will be published only in peer-reviewed journals. The informed consent form will be kept in a locker at the outpatient clinics of the universities of Frankfurt and Dresden.

#### Relevant concomitant care and interventions that are permitted or prohibited during the trial

There is no concomitant care additional to the intervention groups that we already described. If there are medical conditions of the patients, that need to be treated right away, patients will be send to a physician. If patients start a different psychotherapy while being part of the study, they will drop out.

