We based our power analysis on an iterative simulation of increasing sample sizes with starting values of *n* = 30 for the control condition and *n* = 50 for each of the treatment conditions, increasing stepwise by one participant per condition. The variance of the random intercepts and residual variance was set to 0.5 respectively [24]. Because missing values due to the dropout of participants were planned to be imputed by the jump to reference method (J2R) [25], the reference being the control condition, we reduced our expected effected sizes by multiplying them with the term (1—dropout-rate). Given a dropout rate of 26% at post-treatment evaluation in the study by Stolz et al. [16] and a pooled post-treatment dropout rate of 26.2% in a meta-analysis of studies using smartphone apps by Torous et al. [26], we chose a conservative estimate of 30% post-treatment dropout for the APP condition and multiplied the expected effect size of 0.5 by 0.7, equaling to *d* = 0.35. For the TG-APP condition, we expected a lower post-treatment dropout rate of 20% due to the additional guidance by a therapist and multiplied the expected effect size of 0.8 by 0.8, equaling to *d* = 0.64. Based on 500 simulations of the linear mixed model fitted with the expected effect sizes, we obtained the power of finding a statistically significant interaction of group × time based on a likelihood ratio test, compared to finding only main effects, and the 95% confidence interval for this estimate, for increasing sample sizes. We located the minimum sample size in our results after which the lower bound of the 95% confidence interval did not fall below 80% power, given *α* = 0.05. This condition was met at *n* = 41 for the control group and *n* = 61 for both treatment conditions (power estimate = 84%, 95% confidence interval = 80.0, 87.0). In addition to our study purposes, the app provider intends to use the results of the pilot study and the main study for the licensing process of the app as a digital health product. For this licensing process, a separate statistical analysis will be conducted comparing only the APP condition with the WLC condition, using a *t*-test for statistical analysis. A corresponding additional sample size calculation revealed the need to recruit 43 subjects in the wait-list control group (WLC). To establish conformity across the planned analyses we adjusted the number of participants for WLC upward to *n* = 43, resulting in a total sample size of *N* =165 (see also Fig. 1).

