### Eligibility criteria

Inclusion criteria:Current diagnosis of Social Anxiety DisorderWritten informed consent before the start of the studyAge: 18 to 65 yearsPossession of smartphoneFamiliarity with using apps

Exclusion criteria:Acute suicidalityActive substance abuse or dependenceSevere medical conditions (e.g., chronic cardiovascular disease)Severe depressionPsychotic disorderBipolar disorderBorderline personality disorderCurrent psychotherapeutic treatmentCurrent psychopharmacological treatmentNo proficient skills in the German language

Furthermore, patients may be withdrawn from the study for the following reasons:Request of patientPost-hoc observation of criteria for exclusionThreat to patient’s mental or physical health due to participating in the study

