### Statistical methods

#### Sample

All analyses will be conducted in the intent-to-treat (ITT) sample, including all participants that were randomized into one of the three groups.

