#### Drop-out analyses

We define as “drop-out” any participant who did not complete the post-treatment measurement. Systematic differences in dropout rates between the three groups will be analyzed by a Fisher exact test. In addition, differences between participants and drop-outs in terms of sociodemographic and clinical variables will be considered.

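### Making patients who start another psychotherapy drop-outs gives up primary outcomes that could still be measured, which undercuts the all-randomised ITT analysis

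*Protocol article*

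**What the plan says.** Five places in the protocol article bear on this point.

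- *Relevant concomitant care*: "If patients start a different psychotherapy while being part of the study, they will drop out". The rule is mandatory and the same in all three arms.
- *Drop-out analyses*: a drop-out is "any participant who did not complete the post-treatment measurement". Rates are compared between the groups with a Fisher exact test, and drop-outs are compared with the other participants.
- *Statistical methods, Sample*: "All analyses will be conducted in the intent-to-treat (ITT) sample, including all participants that were randomized into one of the three groups".
- *Eligibility criteria*: "patients may be withdrawn from the study for the following reasons". The list includes exclusion criteria that come to light after inclusion. The wording is permissive.
- *Design and sample size*: values missing through dropout are to be filled in by jump-to-reference (J2R) imputation, "the reference being the control condition". Planned post-treatment dropout is 30% in APP and 20% in TG-APP. No figure is given for the wait-list arm (WLC).

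The article does not say whether a patient who leaves under these rules is still interviewed.

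**The concern.** Starting another psychotherapy happens after randomisation and is probably not a chance event. Patients who are doing badly have more reason to look for help, and WLC patients have nothing from the study for three months. If such patients stop being assessed, the observed data become selected for reasons tied to outcome, and perhaps to arm.

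The WLC matters most. It is the comparator for hypothesis 1a and, under J2R, the source of the imputed values. A selected WLC therefore affects its own mean, the values imputed for its own drop-outs, and the values imputed for drop-outs in both active arms.

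The rule also reaches past week 12, because patients remain in the study until follow-up. Hypotheses 1c and 2c claim no significant deterioration between post-treatment and follow-up in the active arms. A patient who deteriorates and seeks therapy in that period is lost from exactly that comparison. Having completed the post-treatment measurement, that patient is not even a drop-out as the drop-out section defines the term.

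**Working it through.** **1. What the provisions do together.** The concomitant-care rule turns the start of other therapy into drop-out, and the drop-out definition equates drop-out with having no post-treatment measurement. So a start before week 12 means no post-treatment LSAS. The ITT sentence keeps the patient in the analysis set, and J2R supplies a value. What is lost is the observation, not the set membership. The Fisher test compares rates and recovers no outcomes.

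**2. How much rests on the WLC reference.** Planned missing post-treatment values are 0.30 × 61 = 18.3 in APP and 0.20 × 61 = 12.2 in TG-APP, about 30 of 122. For WLC nothing can be computed from the article. An assumed 0 to 30% would give 0 to 12.9 of 43.

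**3. Direction.** Three mechanisms act, and they do not agree:
- If WLC leavers would have done worse untreated than those who stay, the retained WLC looks too good and the contrasts shrink.
- If other therapy helps a WLC leaver, J2R replaces a good outcome with an ordinary WLC one. Compared with using the observed value, the contrast grows.
- If other therapy helps a leaver in an active arm, J2R replaces a good outcome with a control-like one, and the contrast shrinks.

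Without rates and outcomes, the net sign is open.

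**4. The plan's own power, as a base.** Inputs from *Design and sample size*: discounted effects 0.5 × 0.7 = 0.35 and 0.8 × 0.8 = 0.64; random-intercept and residual variances 0.5 each; n = 41/61/61; α = 0.05. With two time points the group × time test depends on change scores, whose variance is 2 × 0.5 = 1.

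- Weighted mean effect: (61 × 0.35 + 61 × 0.64) / 163 = 0.3705.
- Noncentrality: Σ nᵢ(dᵢ − 0.3705)² = 10.08.
- Power of the 2-df test (critical value 5.991): 81.9%. Simulations with 20,000 runs gave 81.2 to 81.5%.

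The article states 84% (95% CI 80.0 to 87.0) from 500 runs, so its figure is reproduced within simulation error. At the randomised 43/61/61 the power is 82.9%. This supplies a baseline; it does not itself support or refute the point.

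**5. What following these patients could cost.** Assume a share w of WLC starts other therapy with effect e (0.5 or 0.8 SD, borrowed from the article's own effect sizes), with active-arm means held fixed. Then APP − WLC = 0.35 − w·e and TG-APP − WLC = 0.64 − w·e, at 43/61/61:

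| w (assumed) | APP − WLC | TG-APP − WLC | Interaction power |
|---|---|---|---|
| 5% | 0.31 to 0.325 | 0.60 to 0.615 | 78 to 80% |
| 10% | 0.27 to 0.30 | 0.56 to 0.59 | 72 to 76% |
| 20% | 0.19 to 0.25 | 0.48 to 0.54 | 59 to 69% |
| 30% | 0.11 to 0.20 | 0.40 to 0.49 | 47 to 61% |

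Holding the active arms fixed makes these figures pessimistic. If the J2R reference moved with the WLC mean, the APP contrast at w = 10% would be 0.7 × (0.5 − 0.05) = 0.315 or 0.7 × (0.5 − 0.08) = 0.294.

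**The case against.** The other side has several good arguments.

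- **A reader might infer that the rule contradicts the ITT statement.** It does not. That statement defines who is analysed, and neither withdrawal provision removes anyone from that set. The random-intercept model also keeps patients who have only a baseline value. The tension is with complete follow-up, on which a convincing ITT comparison relies.
- **A reader might infer that patients found ineligible later are removed.** The text only permits withdrawal, and it says nothing about taking them out of the analysis.
- **A reader might take arm-dependent loss as established.** The rule is identical in every arm, and no rate of outside therapy is given. The planned 30% versus 20% difference is put down to therapist guidance. The introduction describes access to treatment as difficult, which argues against high uptake. Arm dependence is plausible, not documented.
- **A reader might put a figure on the bias.** Suppose 15% of WLC and 5% of APP leave, with underlying change 0.5 SD worse. Retained means then give 0.15 × 0.5 − 0.05 × 0.5 = 0.05 SD, or 14% of 0.35. That is a complete-case calculation on assumed inputs. It ignores J2R and divides by an effect already discounted for dropout; against 0.5 it is 10%. In that scenario the APP effect is understated, so the error does not favour the app.
- **The missing interview is inferred.** The article nowhere says that assessment is withheld, and a fuller protocol may keep it. But the mandatory wording and the article's own definition point the same way, and nothing in the text points the other way.
- **Which estimand should be primary is a legitimate choice.** This is true, but an outcome never collected rules out the analysis that uses observed values. Baseline LSAS in the model helps only with loss related to baseline severity, not with loss related to unobserved change.

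**Conclusion.** The point holds as one of avoidable missing data. As written, the protocol gives up obtainable LSAS values after a post-randomisation event, by a mandatory rule for other psychotherapy and by a permissive one for late ineligibility. J2R with WLC as reference and the Fisher test do not recover them. The WLC comparator and the follow-up tests of hypotheses 1c and 2c are the parts most exposed.

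The conclusion rests on reading the concomitant-care rule with the drop-out definition, and on the plausible but undocumented premise that seeking other therapy is related to outcome and arm. The documents support no number and no sign for the bias, and harm to the separate licensing analysis cannot be shown because its handling of missing data is not described. The amendment is worth making because outcomes not collected cannot be recovered later.

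**What to change.** Separate leaving study treatment from leaving assessment.

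- Keep every randomised patient in the planned LSAS and questionnaire assessments at post-treatment and follow-up unless consent is withdrawn, including those who start other psychotherapy and those found ineligible later. Analyse them in the randomised arm.
- Record the start date of any other psychotherapy.
- Report one analysis using the values as observed, and one that sets values after the start of other therapy to missing and imputes them by the planned J2R method. State which is primary.
- Reconcile the sections on sample size, eligibility, analysis sample, drop-out analyses and concomitant care, so that drop-out has one meaning before and after week 12.

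No change to clinical care is proposed. The cost is a short amendment and the effort of keeping visits already planned for all 165 patients. The statistical downside is that observed values include the effect of other therapy. This may dilute the contrasts with WLC and lower power to the extent tabulated above. The second analysis shows how far the result depends on it.

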## Trial status

Recruitment began in July 2022. The current protocol is version 2 of 16 December 2022. There have been no patients enrolled into the trial so far (16 September 2022). Approximate date of completed recruitment: 31 December 2023.

## Data Availability

The data used in this study, including for example, the R code for randomization, are available from the corresponding authors upon reasonable request.

## Abbreviations

LSAS: Liebowitz Social Anxiety Scale
SPIN: Social Phobia Inventory
SPK: Fragebogen zu sozialphobischen Kognitionen
PDI: Pain and Disability Index
BDI-FS: Beck Depression Inventory - Fast Screen
WHO-QOL-BREF: World Health Organization Quality of Life
BSI-18: Brief Symptom Inventory - 18-item version
ACIPS: Anticipatory and Consummatory Interpersonal Pleasure Scale
SPWSS: Social Phobia Weekly Summary Scale
CGI: Clinical Global Impression
QIDS-C: Quick Inventory of Depressive Symptoms
SCID-V: Structured Clinical Interview for DSM-5
Kolb’s LSI: Kolb’s Learning Style Inventory
SPQ-5: Social Pain Questionnaire
CSQ: Client Satisfaction Questionnaire
